### Data management

All case report forms will be checked for errors and missing data before being archived in a study database and all paper-based versions will be locked in a filing cabinet to ensure confidentiality. The primary investigator will have access to the full dataset, in which no information about allocation is visible, and co-investigators will have access as needed. Data management will comply with the rules of the Danish Data Protection Agency. The full protocol will be published, and public access to de-identified patient-level data will be provided once the data have been analyzed. All data will be double entered in Epidata Entry 3.1 (Epidata Associations, Odense, Denmark), range checked for data values, checked against the paper-based assessments and exported to SAS Enterprise Guide 6.4 (SAS Institute Inc., Cary, NC, USA). Data from the *activ*PAL3™ will be downloaded to a computer using *activ*PAL™ Professional Software, version 7.2.32. For each *activ*PAL3™ monitoring the investigators will note the time and date that the monitor is attached to the patient, the time and date that monitoring is started, when the monitor is removed from the patient, and reasons for not wearing the monitor if it is removed prematurely.

### Statistical analyses

#### Descriptive data

Descriptive data for the intervention and control groups will be compared using the chi-square test for categorical variables, the Student’s *t* test for normally distributed continuous variables, and the Mann-Whitney *U* test for non-parametric variables. Descriptive data will be presented as means with standard deviations, medians with inter-quartile ranges or frequencies with percentages depending on the distribution of the variable.

### Primary analysis for the primary outcome

A mixed-model analysis (dif (discharge-baseline), dif (4 weeks-baseline), dif (6 months-baseline)) will be performed using the SAS procedure PROC MIXED. The patient identification number and municipalities will be modeled as random variables, and both group and time will be modeled as fixed factors. The between-group difference in change in DEMMI will be estimated from the interaction between the time and group variable. The primary outcome will be the between-group difference in change in the DEMMI score from baseline to 4 weeks after discharge (end of intervention). The primary analysis will follow the intention-to-treat principle using multiple imputation in case of missing outcome measures and will be unadjusted.

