### Randomization

Patients who consent to participate will be randomly allocated to either of the two groups. Randomization will follow a computer-generated block randomization list produced by the study coordinator (JP). Randomization is stratified within the two participating municipalities. The recruitment will follow a 2:1 allocation in one of the municipalities (A) and a 1:2 allocation in the other municipality (B). This randomization procedure is followed to comply with the capacity of the municipalities (the number of physiotherapists available).

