### Sample size

Based on data from an unpublished cohort study performed at Hvidovre Hospital, 25 consecutively included older medical patients had a mean change in the de Morton Mobility Index (DEMMI) [62] score of 1.8 and a standard deviation of 12.8 from admission to 1 month after discharge. A change of 10 points in the DEMMI score is considered a minimal clinically important difference in acute older medical patients [62]. To be able to detect a 10-point difference in the between-group change in the DEMMI score at the 4-week assessment (primary end point), we will need a sample size of 27 patients per study arm to obtain a type I error rate of 5 % and a power of 80 % for a two-sample *t* test of a normal mean difference with a two-sided significance level. We will continue to recruit patients until 54 patients have been assessed for the primary end point (4 weeks). In case of a skewed distribution of patients in the two groups (intervention and control), we will recruit until both groups contain 25 patients. We expect a maximum of 80 patients to be included in the study.

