### Secondary and supplementary analyses

From the primary analysis model, the effect during hospitalization and the post-intervention effect (change from 4 weeks to 6 months post discharge) will be estimated. For the secondary outcomes, similar analyses will be performed. Moreover, all analyses will be using adjustments for baseline DEMMI. To account for imbalances in in-hospital time, a sub-analysis will be performed for the effect during hospitalization and the effect from baseline to end of intervention adjusted for length of stay. Additionally, the unadjusted repeated model will be carried out following the per protocol principle, comparing patients who have fulfilled the compliance criteria with the control group. All between-group differences will be expressed as the average difference in change from baseline. The analyses outlined above will all be reported in the main trial manuscript regarding effect of the strength training program.

If additional funding is obtained, more patients will be included to increase the sample size to obtain sufficient power to model statistical interactions and perform secondary analyses (described below), which will be published subsequently. To investigate the possible influence of confounders and modifiers on the effect of the intervention on DEMMI, an unadjusted analysis of variance of the between-group change from baseline to 4 weeks post discharge in the DEMMI score will be performed. In addition, this model will be extended by adjusting for all and each of the potential confounders and modifiers one by one. Confounding effects will be evaluated by comparing the unadjusted effect of group with the adjusted effects. Moreover, to investigate whether or not the effect of the intervention is modified by the potential confounders and modifiers the adjusted models will be extended with an interaction term between group and the potential confounders and modifiers. Similar analysis will be performed with 24-h mobility (average time spent standing or walking per 24 h) and with those of the secondary outcomes that showed a significant between-group difference in the primary analysis. Also, a logistic regression with compliance as the outcome and each of the potential confounders and modifiers as covariates will be performed. All analyses will follow both the intention-to-treat and the per protocol principle.

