To investigate the effect of the intervention on cognition (MCI status, MMSE, OMC, HVLT, DSST, Trails A and B) at 4 weeks, the following analyses will be performed. A generalized logistic regression for MCI status and an analysis of variance for MMSE, OMC, HVLT, DSST, and Trails A and B will be used with group as the independent variable. The analyses will follow the intention-to-treat principle with multiple imputation for missing values. Moreover, these analyses will also be performed adjusting for baseline OMC, baseline DEMMI, gender and age, depression, health status, nutritional state, self-reported physical activity, pain, medications, length of stay and 24-h mobility using assessments from the first week after discharge, and possible interactions with group will be analyzed. Additionally, the models will be repeated following the per protocol principle comparing patients. All results will be expressed as estimated means’ differences between the intervention and control group with the corresponding 95 % confidence intervals.

All models will be investigated for goodness-of-fit (linearity, variance homogeneity and normal distribution of residuals) by visual inspection of plots and remodeling will be performed accordingly. All statistical tests will be performed using SAS (SAS Institute Inc., Cary, NC, USA) and *p* values ≤0.05 will be considered statistically significant. However, for all analyses evaluating potential modifiers and confounders of the intervention *p* values ≤0.01 will be used to account for multiple testing. No interim analysis will be made.

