### Changes to initial plan

In the statistical analysis plan, imputation for missing data was changed from “last observation carried forward” to “multiple imputation.” This protocol change was made before inclusion was completed, and while the study was still blinded. The BI was added as a secondary outcome before inclusion of the first patient to enable comparison with previous studies evaluating ADL during and after hospitalization [9, 10, 17, 109].

From February 2014, patients have been included from an additional municipality, the municipality of Hvidovre, due to the possibility of providing in-home training for these patients as well. Randomization in this municipality follows a 2:2 allocation. From September 2014, patients assigned to physical rehabilitation in the community have no longer been excluded from the study, as rehabilitation in the community is rarely commenced until 4 weeks after discharge and thus after the study’s primary end point. From January 2015, a physician has performed the initial screening of all eligible patients and informed the patients about the study before referring them to the primary investigator for informed consent and baseline assessments to enhance enrollment.

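### Allocation ratios differ by municipality, so municipality should be a fixed stratification factor in the analyses rather than a random effect with two or three levels

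*Protocol article*

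**What the plan says.** - **Allocation.** The Randomization section stratifies by municipality, with ratios chosen to suit physiotherapist capacity: "The recruitment will follow a 2:1 allocation in one of the municipalities (A) and a 1:2 allocation in the other municipality (B"). Changes to initial plan adds the municipality of Hvidovre from February 2014: "Randomization in this municipality follows a 2:2 allocation".
- **Primary model.** Primary analysis for the primary outcome specifies a mixed model of the changes from baseline at discharge, 4 weeks and 6 months. Group and time are fixed, and "The patient identification number and municipalities will be modeled as random variables". The analysis is otherwise described as unadjusted.
- **Analyses that reuse it.** Under Secondary and supplementary analyses, the secondary outcomes get analyses similar to the primary one, and the per-protocol analysis repeats the same repeated-measures model. Municipality stays in both.
- **Analyses without it.** The second paragraph of that section, which begins by making further analyses depend on additional funding, plans a confounder and modifier investigation that starts from "an unadjusted analysis of variance of the between-group change from baseline to 4 weeks post discharge in the DEMMI score will be performed". The cognition models "will be used with group as the independent variable". Neither names a municipality term, and municipality is not among the possible confounders in Table 2 or under Additional variables.
- **Sample size.** "we will need a sample size of 27 patients per study arm", for a "type I error rate of 5" % and 80% power, from a two-sample t "test of a normal mean difference with a two-sided significance level". The calculation takes no account of the strata.

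**The concern.** In a stratified trial with the same ratio in every stratum, leaving the stratum out of the model costs some precision but does not bias the effect. Here the chance of receiving the intervention depends on the municipality, so the arms differ systematically in municipality mix. Randomization protects the comparison within each municipality, not the pooled one. If recovery differs between municipalities, through their populations or their municipal services, part of that difference enters any estimate that does not condition on municipality.

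A random intercept conditions only partly. It shrinks the municipality effects towards zero by an amount set by an estimated variance, and two or three levels can hardly estimate that variance. When it is estimated as zero, the municipality adjustment vanishes and the model becomes the pooled comparison. A single intercept per municipality also does not vary with time, whereas the primary estimate is specific to 4 weeks.

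At stake are a small avoidable bias in the primary result, a larger one in the later exploratory analyses, and a power statement that does not describe the analysis best suited to this design.

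**Working it through.** **Inputs.** From Sample size: difference 10 points, SD of change 12.8, two-sided 5%, 27 per arm, 54 assessed. From Randomization and Changes to initial plan: ratios 2:1, 1:2 and 2:2. Assumed, because the protocol gives neither: the share of patients per municipality, and the municipality difference in mean DEMMI change (0 to 10 points). The protocol does not say which arm the first number of a ratio refers to, so the direction of any bias is open; its size is not affected.

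**1. The plan's own figure.** Information for a two-group comparison is n1·n2/(n1+n2) = 27·27/54 = 13.5. Noncentrality = (10/12.8)·√13.5 = 2.87 with 52 df, which gives power 80.4%. At 26 per arm it is 78.9%. So 27 per arm is exact for a plain 1:1 t test.

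**2. Association between arm and municipality.** The bias of an estimate without municipality is the between-arm difference in A's share times the A–B difference in recovery (in the three-municipality layout the third is split equally and drops out).

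| Layout of 54 | A's share, one arm | A's share, other arm | Difference |
|---|---|---|---|
| 18/9 + 9/18 | 18/27 = 66.7% | 9/27 = 33.3% | 33.3% |
| A:B split 80:20 | 88.9% | 66.7% | 22.2% |
| 12/6 + 6/12 + 9/9 | 12/27 = 44.4% | 6/27 = 22.2% | 22.2% |

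An A–B difference of 5 points gives a bias of 5/3 = 1.7 points in the first layout and 5·0.222 = 1.1 in the third. A difference of 10 points gives 3.3 and 2.2. These figures apply to the analyses with no municipality term.

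**3. The planned random effect.** Simulation of the 4-week change only, SD 12.8, REML, 1,500 trials per scenario. The first value in each cell is with no treatment effect, the second with a 10-point effect. The random-effect test used n−2 df.

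| Layout, A–B difference | Variance estimated as zero | Bias, no term | Bias, random | Bias, fixed |
|---|---|---|---|---|
| 18/9 + 9/18, 0 | 68%, 68% | 0.13, 0.01 | 0.16, 0.02 | 0.17, −0.01 |
| same, 3 | 53%, 54% | 1.06, 0.90 | 0.52, 0.35 | 0.07, −0.10 |
| same, 5 | 36%, 36% | 1.67, 1.78 | 0.62, 0.72 | 0.02, 0.14 |
| same, 10 | 4%, 5% | 3.63, 3.39 | 0.79, 0.59 | 0.28, 0.08 |
| 14/7 + 7/14 + 6/6, 5 (third midway) | 40%, 40% | 1.24, 1.23 | 0.58, 0.56 | −0.04, −0.05 |

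The non-zero values for the fixed factor are simulation error: its standard error is 12.8/√12 = 3.70 per trial, so 3.70/√1500 = 0.10 for a mean. Subtracting the fixed from the random column, which share that error, leaves about 0.4 to 0.6 points wherever municipalities differ (for example 0.62 − 0.02 = 0.60 and 0.79 − 0.28 = 0.51).

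Type I error of the random-effect model was 5.0–6.4% and its power 79–83%. For the fixed factor these were 4.3–5.3% and 75–76%. With no municipality term, type I error reached 14% at a 10-point difference.

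**4. Power with municipality fixed.** Information is the sum over municipalities of n1·n2/(n1+n2).

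- A and B only: 18·9/27 + 9·18/27 = 12.0, which is 12/13.5 = 8/9 of the plan's. Noncentrality (10/12.8)·√12 = 2.71, df 51, power 75.7%. The A/B split does not matter, since each patient contributes (2/3)(1/3) = 2/9. The difference detectable with 80% power is about 10.6 points.
- One third of patients in the 2:2 municipality: 12·6/18 + 6·12/18 + 9·9/18 = 12.5. Noncentrality 2.76, df 50, power 77.3%. With one fifth there, 76.6%.
- 60 assessed, A and B only: 60·2/9 = 13.3, df 57, power 80.1%.

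**The case against.** The planned primary model does include municipality, and most of the adjustment happens. At a 10-point difference it cuts a bias of about 3.3 points to well under 1. Type I error stays near 5–6%, and the remaining bias is small beside the 10-point target and the SD of 12.8. This stands, and it limits the weight of the point.

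The size of any municipality effect is unknown. The outcome is change from baseline, so constant differences in mobility level cancel and only differences in recovery matter. All patients enter through one Emergency Department, and Study setting describes care as uniform for all citizens. A 10-point difference in recovery would equal the minimal clinically important difference, while the pilot cohort's mean change was 1.8. This also stands: the 5- and 10-point cases are illustrations, not estimates.

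Two stronger readings are tempting and are not supported.

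- A reader might infer that the trial as planned fails to deliver 80% power. It does not follow. The stated figure reproduces, and the planned random-effect model roughly keeps it in simulation. The 76–77% arises only once municipality is fixed, at SD 12.8 and 54 assessed. That SD comes from 25 patients not split by municipality and may already contain between-municipality variance. The repeated-measures model and the planned adjustment for baseline DEMMI may regain precision.
- A reader might infer that municipality is dropped from the secondary-outcome and per-protocol analyses. It is not, because both reuse the primary model. It is unnamed only in the DEMMI analysis-of-variance and modifier work and in the cognition models. The protocol introduces the former as conditional on additional funding. The cognition paragraph follows and is read here as part of the same block.

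What the objection does not answer is why a factor that is tied to treatment by design, with two or three known levels, should be left to a poorly estimated variance when a fixed term removes the problem.

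**Conclusion.** The point holds as an inexpensive improvement, not as a fault that invalidates the primary analysis. Arm and municipality are associated by design. The planned random effect removes most but not all of the consequence: about 0.4–0.8 DEMMI points of bias remain when municipalities differ in recovery by 3 to 10 points, and essentially none with a fixed factor. The analyses that name no municipality term would carry one third of any A–B difference with two equal strata, and about 22% of it if a third of patients come from the 2:2 municipality.

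These results rest on assumed municipality differences and shares, and on a simulation of the 4-week change alone rather than the full repeated-measures model. If municipalities do not differ in recovery, there is no bias under any of the models.

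**What to change.** 1. In the primary model, fit municipality as a fixed stratification factor with all three levels, together with municipality by time. The secondary-outcome and per-protocol models that reuse it then inherit the change.
2. Add the same fixed factor to the DEMMI analysis-of-variance and modifier models, to the cognition models, and to the multiple-imputation model.
3. Keep 27 per arm as the result for a plain 1:1 t test, and add that with municipality fixed and 54 assessed the power for 10 points is about 76–77%, or 80% for about 10.6 points with A and B only, before any gain from baseline adjustment or repeated measures. If 80% for 10 points is wanted without relying on such gains, about 60 assessed patients suffice, which is within the expected maximum of 80 included.

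The cost is wording, 1–2 degrees of freedom per time point and a slightly lower stated power. No new data are needed, and Study status reports recruitment as still ongoing, so the change can be made before allocation is revealed.

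### Random patient and municipality effects, with no residual structure named, imply one common variance for the three change scores, so the standard error of the primary 4-week difference is not built on the 4-week variance

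*Protocol article*

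**What the plan says.** The section on the primary analysis of the primary outcome in the protocol article states: "A mixed-model analysis (dif (discharge-baseline), dif (4 weeks-baseline), dif (6 months-baseline)) will be performed using the SAS procedure PROC MIXED". On the random part it says "The patient identification number and municipalities will be modeled as random variables", and on the fixed part "both group and time will be modeled as fixed factors". The between-group difference comes from the group-by-time interaction, and the primary contrast is the one at 4 weeks. The analysis is by intention to treat, "using multiple imputation in case of missing outcome measures and will be unadjusted".

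The section on secondary and supplementary analyses takes the effect during hospitalization from the same model and plans similar analyses for the secondary outcomes. It also sets the model check: "All models will be investigated for goodness-of-fit (linearity, variance homogeneity and normal distribution of residuals) by visual inspection of plots and remodeling will be performed" as the plots suggest. No alternative model is named.

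The sample size section gives one relevant SD: 12.8 for the change from admission to 1 month, from 25 patients in an unpublished cohort. It uses this SD in a two-sample t test.

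**The concern.** A patient random intercept with independent, equal-variance residuals is compound symmetry. The municipality effect adds a covariance shared by all visits and does not relax it. The model then treats the change over the hospital stay, the change to 4 weeks and the change to 6 months as equally variable and equally correlated. These changes cover very different spans, so equal variances are not something to take for granted.

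At stake is the standard error of the primary contrast, and with it the confidence interval and p value. They would depend partly on how variable the discharge and 6-month changes turn out to be, although neither visit is part of the primary question. The sample size calculation uses the 4-week variance alone, so the planned test and the powered test would have different standard errors.

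**Working it through.** **Inputs from the protocol (sample size section).** Difference to detect 10 points; SD of change to 1 month 12.8; 27 per arm; two-sided 5%; power 80%.

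**Inputs assumed, because the protocol does not give them.** SDs of change at discharge and at 6 months (varied below) and a correlation of 0.6 between change scores. The calculations take equal arms and complete data, and leave out the municipality term.

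**The plan's own figure.** With SD 12.8 and a difference of 10, the noncentral t distribution gives power 78.9% at 26 per arm and 80.4% at 27. The stated 27 per arm reproduces. The standard error behind it is 12.8 × √(2/27) = 3.48.

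**What the model uses instead.** With complete data and a group-by-time mean model:

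- sampling SE at 4 weeks = √(4-week variance × 2/27)
- model SE under compound symmetry = √(mean of the three visit variances × 2/27), the same at every visit

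A REML random-intercept fit to one simulated data set (true SDs 8, 12.8, 12.8) confirms this. The model SE was 3.173 at all three visits, equal to the averaged-variance formula. The SEs from each visit's own variance were 2.385, 3.507 and 3.493.

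**Numbers for the 4-week contrast.** The 4-week variance is 12.8² = 163.84 throughout. For SDs of 8 at discharge and 12.8 at 6 months, the mean variance is (64 + 163.84 + 163.84)/3 = 130.56, its root is 11.43, and 11.43/12.8 = 0.893. The other rows follow in the same way. Type I error is from 40,000 simulated trials per case.

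| Assumed SD, discharge / 6 months | Mean variance | Model SE | Ratio to 3.48 | Type I error, compound symmetry | Type I error, unstructured |
|---|---|---|---|---|---|
| 8 / 12.8 | 130.56 | 3.11 | 0.893 | 7.9% | 4.8% |
| 9 / 14 | 146.95 | 3.30 | 0.947 | 6.2% | 4.9% |
| 9 / 16 | 166.95 | 3.52 | 1.009 | 4.9% | 5.1% |
| 12.8 / 18 | 217.23 | 4.01 | 1.151 | 2.5% | 5.0% |

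In the last case simulated power was 71.7% under compound symmetry and 80.3% under an unstructured covariance. A separate set of 20,000-trial simulations gave 71.3% and 79.7% for that case, and a type I error of 8.0% for the first.

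**The in-hospital effect from the same model.** With a discharge SD of 8 and a 6-month SD of 12.8, the correct SE is 8 × √(2/27) = 2.18, but the model would report 3.11. The ratio is 11.43/8 = 1.43, so the SE is about 43% too large.

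**The case against.** Four points on the other side carry weight.

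- **The residual structure is not stated.** The article names two random effects and does not mention the residuals. PROC MIXED can combine random effects with a repeated-measures residual structure, and the article elsewhere calls this a repeated model. A reader might infer that the plan has definitely committed to compound symmetry. The text does not say so; that is what the stated terms imply if nothing is added. An analysis plan that is not shown may add to them.
- **The assumption is to be checked.** Variance homogeneity is on the list of checks, and a marked difference between visits could be seen and acted on. This softens the point. It does not remove it, because the check is visual, follows the data and names no alternative, so the primary model would be chosen with the results at hand.
- **Missing visits.** A reader might infer that a wrong correlation structure also weights the observed visits wrongly. Multiple imputation is planned, so each analysed data set is complete, and that argument falls away.
- **The size rests on assumed SDs.** The two largest errors in the table arise where one of the other visits has the same SD as 4 weeks. Where the SD rises at every visit, the errors partly or wholly cancel (6.2% and 4.9%). The simulations also omit multiple imputation, the municipality term and the unequal allocation within municipalities, so they illustrate the mechanism and do not predict the trial's error rates.

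**Conclusion.** The point holds in limited form. With random patient and municipality effects and no residual structure named, the model implies a common variance and correlation across the three changes. The 4-week standard error then averages three visit variances. Under the assumed SDs its error runs from about -11% through about zero to about +15%. These cases are illustrations, not bounds. If the three variances average to the 4-week variance, there is no error.

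A reader might infer that the primary test is anti-conservative, or that the treatment estimate is biased. The documents support neither. They give only the 4-week SD, so the direction cannot be determined. With complete data and the municipality term set aside, the estimated 4-week difference is the same under either covariance. The stated sample size is not in dispute. What remains is an avoidable dependence of the primary p value on two other visits. It is worth correcting because an assumption-free alternative for three visits is easily affordable.

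**What to change.** Prespecify an unstructured within-patient covariance over the three visits in place of the patient random intercept. In PROC MIXED this is REPEATED time / SUBJECT=patient TYPE=UN, with Kenward-Roger degrees of freedom. Leave the municipality term as planned and take the 4-week between-group contrast from this model. If it does not converge, fall back to a structure that still lets the variance differ by visit, such as TYPE=CSH. Homogeneous compound symmetry should not be the fallback, since it restores the same problem. State this before unblinding, so that the primary covariance does not depend on the inspection of plots.

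The cost is one line of code and one sentence. The unstructured matrix has six covariance parameters, against two for a random intercept with a common residual variance, estimated from 54 or more patients. If an analysis plan already sets such a structure, saying so in one sentence is enough.

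### The primary DEMMI analysis is an unadjusted change score with the baseline-adjusted model only supplementary, and secondary outcomes have no own-baseline covariate: valid, but precision is forgone

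*Protocol article*

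**What the plan says.** Under Primary analysis for the primary outcome, the response is the difference from baseline at discharge, 4 weeks and 6 months. Group and time are fixed effects; patient and municipality are random. Missing outcomes are handled "using multiple imputation in case of missing outcome measures and will be unadjusted".

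Under Secondary and supplementary analyses, secondary outcomes get the same kind of model, followed by: "Moreover, all analyses will be using adjustments for baseline DEMMI". No other baseline value is named as a covariate for these analyses. All effects are reported as differences in change from baseline, and this set of analyses is promised for the main trial manuscript.

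Study sample and recruitment procedure places baseline assessment before randomization. Table 2 schedules a baseline for DEMMI and for all six secondary outcomes. Additional variables lists baseline DEMMI as a possible confounder and modifier.

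The sample size rests on "a standard deviation of 12.8 from admission to 1 month after discharge", a 10-point difference in change and a "two-sample *t* test of a normal mean difference with a two-sided significance level", giving "we will need a sample size of 27 patients per study arm".

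**The concern.** A change score fixes the slope of follow-up on baseline at 1. Here baseline is taken in the first 48 hours of an acute admission, deliberately before treatment has had much effect, and follow-up is at home 4 weeks after discharge on a scale that stops at 100. A slope below 1 is plausible. If so, a group that starts lower by chance will tend to show more improvement, and the change-score comparison credits part of that to treatment. With 54 assessed patients, such imbalance is not rare.

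Using baseline DEMMI as a covariate estimates the slope instead of fixing it. The authors evidently think this worthwhile, because they plan the adjusted analysis, but the result that decides the trial is the unadjusted one.

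For knee extension strength, the sit-to-stand test, gait speed, grip strength and the Barthel Index, the planned covariate is the baseline of a different measure. Regression to the mean and chance imbalance in the outcome itself are then addressed only as far as its baseline correlates with DEMMI.

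**Working it through.** **Inputs from the article (Sample size).** Difference 10 points; SD of change 12.8; "a type I error rate of 5 % and a power of 80" per cent; two-sided two-sample t test; 27 per arm.

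**Not in the article, so assumed.** The correlation r between baseline and 4-week DEMMI, and the raw SD at each visit.

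**Step 1: the plan's own figure.** The normal approximation gives 26 per arm. The noncentral t distribution gives 27, with power 80.4%. The stated size reproduces, and it matches the unadjusted analysis because 12.8 is the SD of the change. If both arms held only 25, the minimum set for skewed groups, power would be 77.2%.

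**Step 2: variance with adjustment, equal SDs.** With common raw SD s:

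- variance of change = 2s²(1 − r)
- residual variance after adjustment = s²(1 − r²)
- ratio = (1 + r)/2, so the reduction is (1 − r)/2
- adjusted SD = 12.8 × √((1 + r)/2)
- raw SD implied by the plan's figure: s = 12.8/√(2(1 − r))

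Power and sample size are from the noncentral t distribution. The degree of freedom spent on the covariate is ignored.

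| r | implied raw SD | variance reduction | adjusted SD | power at 27 per arm | n per arm for 80% |
|---|---|---|---|---|---|
| unadjusted | – | – | 12.80 | 80.4% | 27 |
| 0.5 | 12.8 | 25% | 11.09 | 90.2% | 21 |
| 0.6 | 14.3 | 20% | 11.45 | 88.3% | 22 |
| 0.7 | 16.5 | 15% | 11.80 | 86.3% | 23 |
| 0.8 | 20.2 | 10% | 12.14 | 84.4% | 25 |
| 0.9 | 28.6 | 5% | 12.48 | 82.4% | 26 |

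**Step 3: unequal SDs.** With k = follow-up SD / baseline SD, the reduction is 1 − k²(1 − r²)/(1 + k² − 2rk).

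| r | k = 0.8 | k = 1.0 | k = 1.2 |
|---|---|---|---|
| 0.5 | 42.9% | 25% | 12.9% |
| 0.6 | 39.8% | 20% | 7.8% |
| 0.7 | 37.2% | 15% | 3.4% |
| 0.8 | 36.0% | 10% | 0.3% |

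The regression slope is r × k, and the gain vanishes as it approaches 1: at k = 1.2 and r = 0.8 the slope is 0.96 and the gain 0.3%.

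**Step 4: chance imbalance, equal SDs.** One standard error of the baseline difference between arms is s√(2/27). The resulting shift in the change-score effect is (1 − r) times that. The values of s and r must agree with the change SD of 12.8:

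- r = 0.5, s = 12.8: 0.5 × 12.8 × 0.272 = 1.7 points
- s = 15, so r = 1 − 12.8²/(2 × 15²) = 0.64: 0.36 × 15 × 0.272 = 1.5 points
- r = 0.8, s = 20.2: 0.2 × 20.2 × 0.272 = 1.1 points

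A one-standard-error imbalance therefore moves the estimate by about 1 to 2 points, against a target difference of 10.

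**Step 5: secondary outcomes.** The article gives no SD or correlation for any of them, nor their correlation with baseline DEMMI. No figure can be calculated, and the DEMMI range above does not carry over.

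**The case against.** The strongest defence is that nothing in the primary analysis is invalid. Baseline precedes randomization, so the change-score comparison is unbiased over repeated randomizations. The trial was sized for "To be able to detect a 10-point difference in the between-group change in the DEMMI score at the 4-week assessment" using the SD of that same quantity. The adjusted DEMMI analysis will be carried out and published. All of this stands, and it rules out several stronger readings that a reader might infer:

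- *The trial is underpowered because of this choice.* No: 27 per arm meets the stated 80%. What is lost is additional precision.
- *The primary estimate is biased.* No: the shift in Step 4 is conditional on the imbalance that happens to arise, and averages to zero.
- *Baseline adjustment has been left out.* No: it is planned; only its rank is at issue.
- *Adjustment always gains when the correlation is below 1.* This holds with equal SDs. The general condition is a slope other than 1, and Step 3 shows cases with almost no gain.
- *The secondary outcomes ignore their own baselines.* No: they are analysed as change from baseline. What is missing is the own baseline as a covariate.
- *The two sections contradict each other, one saying unadjusted and the other adjusting all analyses.* The second sentence stands under the supplementary heading and reads most naturally as an additional adjusted set, although the text should say so.

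It is also true that the fix leaves two DEMMI analyses with their labels exchanged. The label matters, however: in a trial this small the two may disagree, and the plan then commits the authors to the one that is generally less precise.

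**Conclusion.** The point holds as a matter of efficiency and of protection against chance imbalance, and the plan should be changed. The deciding analysis sets aside a covariate measured before randomization that the authors already intend to use elsewhere.

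For DEMMI, a variance reduction of 25% to 10% and power of about 90% to 84% instead of 80.4% rest on two assumptions the article does not supply: equal SDs at the two visits and r between 0.5 and 0.8. Allowing the follow-up/baseline SD ratio to be 1.2 or 0.8 widens the reduction to about 0–13% or 36–43% respectively. The direction is secure, because in large samples adjustment is never less precise than the change score; here its cost is negligible.

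For the secondary outcomes the specification is poorly chosen, but the loss cannot be quantified from the article.

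**What to change.** Before unblinding:

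1. In Primary analysis for the primary outcome, make the baseline-adjusted model primary: add baseline DEMMI and its interaction with time as fixed effects in the PROC MIXED model. Report the unadjusted change analysis as a sensitivity analysis.
2. In Secondary and supplementary analyses, replace the blanket adjustment for baseline DEMMI with adjustment of each secondary outcome for its own baseline, where that was measured before randomization. Check this for 24-h mobility: the monitor is worn during the hospital stay, so its baseline value may overlap the in-hospital training.
3. State which analyses are unadjusted and which adjusted, so that the two sections cannot be read against each other.

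The cost is about one degree of freedom per visit and a change of wording; no new data are needed. The article reports recruitment as ongoing, and under Changes to initial plan it records an earlier change to the analysis plan made while the study was blinded, so the same route is open if the data are still blinded.
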